#### UCLA Loneliness Scale

Loneliness will be assessed using the UCLA Loneliness Scale [35]. The UCLA Loneliness Scale is a well-validated and widely used tool designed to measure subjective feelings of loneliness and social isolation. It evaluates the overall sense of loneliness through 20 items that reflect social isolation and dissatisfaction with one’s social relationships [35]. Participants will be asked to rate each item on a 4-point Likert scale, ranging from 1 (never) and 2 (rarely) to 3 (sometimes) and 4 (often), with higher scores indicating greater loneliness. The total score will be derived by summing the responses across all items, with possible scores ranging from 20 to 80. In this study, loneliness will be treated as a continuous variable. The UCLA Loneliness Scale demonstrates high internal consistency and strong construct validity, correlating well with other measures of loneliness and social well-being [35].

#### Apathy Evaluation Scale

Apathy will be assessed using the Apathy Evaluation Scale (AES), a validated 18-item tool designed to measure the cognitive, behavioral, and emotional aspects of apathy [36]. Items are scored on a 4-point Likert scale, and higher scores indicate greater levels of apathy. The AES shows high internal consistency and good validity, with strong correlations to other measures of mood and motivation, distinguishing apathy from related conditions such as depression [36].

### Secondary Outcomes

Secondary outcomes will be examined as potential mediators of effects between RT, loneliness, and apathy.

#### Cognition

Cognition will be measured by the telephone Montreal Cognitive Assessment (T-MoCA). The T-MoCA is a validated tool designed to screen for MCI across domains such as attention, memory, language, visuospatial skills, executive function, and orientation [37,38]. Adapted from the original Montreal Cognitive Assessment for remote administration, the T-MoCA is particularly useful for populations where in-person assessments may be challenging. The T-MoCA consists of 22 items and participants will be scored out of 22 points, with a score below 18 typically indicating cognitive impairment. The T-MoCA has shown good reliability and validity that is concurrent with the original in-person Montreal Cognitive Assessment [37].

#### PROMIS: Meaning and Purpose

Meaning and purpose in life will be assessed using the PROMIS (Patient-Reported Outcomes Measurement Information System) Meaning and Purpose Scale. The PROMIS Meaning and Purpose Scale is a validated tool that measures an individual’s sense of purpose, significance, and meaning in life. This scale will assess the extent to which individuals feel their lives are filled with meaning, direction, and goals, contributing to overall well-being and mental health. Participants will respond to a series of items on a 5-point Likert scale, entailing 1 (never), 2 (rarely), 3 (sometimes), 4 (often), and 5 (always), with higher scores indicating a stronger sense of meaning and purpose. PROMIS provides a reliable and valid measure of meaning in life, demonstrating internal consistency across diverse populations [39]. It also shows strong correlations with other related constructs, such as life satisfaction and psychological well-being, reinforcing its construct validity [39].

#### Geriatric Depression Scale

Depressive symptoms will be assessed using the Geriatric Depression Scale–Short Form (GDS-SF) [40]. The GDS-SF is a widely validated screening tool for depressive symptoms in older adults. It is a shortened version of the original 30-item GDS and contains 15 dichotomous (yes or no) questions designed to assess mood and affect, with a focus on identifying symptoms of depression in the older adult population [40]. Scores range from 0 to 15, with higher scores indicating greater depressive symptoms. The GDS-SF is validated in multiple populations, with good internal consistency and strong concurrent validity when compared to other depression scales such as the Hamilton Depression Rating Scale (HDRS) [41].

#### MOS Social Support Scale

Social support will be assessed using the Medical Outcomes Study (MOS) Social Support Survey [42]. The MOS Social Support Scale is a widely used 19-item instrument designed to measure various dimensions of social support, including emotional, informational, tangible, affectionate, and positive social interaction. Items are rated on a 5-point Likert scale ranging from 1 (none of the time) to 5 (all of the time), with higher scores indicating greater perceived social support. The MOS Social Support Scale was validated across diverse populations, demonstrating high internal consistency and strong construct validity, with robust correlations to other measures of social functioning and mental health [42].

#### Covariates

Covariates were selected based on their reported associations with cognition, social connection, and overall health. Covariate data will be used to describe the population engaged in the study and will be informative in terms of feasibility and generalizability. Age will be recorded in years, calculated from the self-reported date of birth, as age influences cognitive decline [43]. Gender will be categorized as male or female based on self-report, considering that gender differences influence cognitive performance and vulnerability to cognitive decline [44]. Race will be self-reported and classified into categories to explore potential disparities in health outcomes, as prior studies highlight the role of race in health inequalities. Education, assessed in years of formal schooling completed, will be collected through self-report, as increased educational attainment is associated with better cognitive function and social engagement in older adults [45]. Participants will also self-report their occupation before retirement, recognizing that work-related activities can provide cognitive stimulation and social interaction, which impact mental health outcomes. Marital status will be evaluated at baseline, with responses categorized as never married, married, widowed, divorced, or separated, given that marital status is linked to social support and well-being, crucial for cognitive health [46]. Living arrangements will be documented to differentiate those living alone, with family, or in institutional settings, as prior studies suggest that living arrangements can affect loneliness and access to social networks [47]. Social determinants of health including transportation and housing will be assessed via self-report. The FRAIL Scale will be used to assess frailty through self-reported items related to fatigue, resistance, ambulation, illness, and weight loss, recognizing that frailty is associated with cognitive decline and increased risk for adverse health outcomes in older adults [48] and both loneliness and apathy are associated with frailty and functional decline [49,50]. Finally, overall health and comorbidities will be self-reported and supplemented by information from the electronic health record, encompassing chronic conditions such as diabetes, hypertension, and cardiovascular diseases, which have known associations with cognitive impairment and social functioning.

#### Feasibility Outcomes

Feasibility will be determined by screening, enrollment, and acceptability of the intervention. Acceptability of the intervention will also be assessed via program satisfaction surveys (eg, satisfaction, mood, belonging, connection with members) at 3 months and 6 months as well as qualitative interviews to explore program acceptability, barriers and facilitators of participation, and technology accessibility. Outcome measures including feasibility and health outcomes are detailed in Textbox 1 and Table 2. Benchmarks are determined by prior LSC metrics and expectations for recruitment, enrollment, and participation based on prior LSC participants. The metrics we propose are based on study-specific retention efforts (eg, preintervention counseling, relationship building with participants, and participant incentives).

Feasibility outcomes.
**Criteria**
ScreeningEnrollmentAcceptabilityProgram evaluationBarriers and facilitatorsTechnology access
**Benchmarks**
No. of individuals screened/total referred (≥70% good)No. of individuals who agree/total screened (≥70 good)No. of individuals who complete 9/12 visits/total enrolled (≥70 good)SurveyOpen-ended interviewOpen-ended interview

**Table 2 table2:** Outcome measures.

Outcome measures			Assessment		Metrics

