#### Intervention

LSC is a virtual, social storytelling space for older adults aged 60 and older where members can share life stories and connect with other members to promote a sense of belonging, purpose, and meaning. Clubs include up to 15 members that meet once a week for 1 hour. The number of participants per group is determined based on past levels of participation where 10-15 individuals are recruited per group and 6-8 attend each session due to the nature of the population (eg, multimorbidity and acute illness). The protocol for the study will not deviate from routine LSC protocols and will be offered similarly to the usual schedule and prompts as described in the introduction except for dedicated recording sessions which will be replaced by a usual session (Table 1). Clubs are led by a nonclinician facilitator who offers prompts to trigger discussion and reminiscence. Sessions begin with greetings after which 2 prompts are offered by the facilitator. The facilitator manages the group to encourage participation by all members. To promote technology equity (colloquially referred to as “techquity”), LSC has been delivered via live video or telephone according to participant preference to promote technology inclusiveness. Participants for this study will have the option to use video or telephone based on preference. The primary endpoint for this study will be 3 months based on durations of other RT interventions [31,34]. We will additionally collect assessment data at 6 months to preliminarily determine the feasibility and efficacy of a 6-month intervention in participants who continue to participate in the intervention over a longer period. Fidelity will be assessed via periods of observation by research staff to observe if components of the intervention are met (eg, 2 prompts per session and individual participation).

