### Data Collection

Assessments will be collected via telephone at baseline, 3 months, and 6 months post RT. Participants will receive a gift card for each completed assessment. Qualitative interviews will be conducted with a subset of 30 participants to assess satisfaction with the intervention, what aspects can be improved, and explore barriers and facilitators of participation, including digital literacy. A semistructured interview guide is included in Multimedia Appendix 1. Interviews will take place at an agreed-upon location over 60 minutes and will be conducted by the primary investigator or coinvestigator. We will collect data on the following outcome measures and covariates:

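### The enrolment benchmark counts people excluded at screening against the study, and the 70% target for completing 9 of 12 sessions sits well above the only past attendance figure shown

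*Protocol article*

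**What the plan says.** The benchmarks are in Textbox 1 of the protocol article, under Feasibility Outcomes.

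- **Enrolment:** "No. of individuals who agree/total screened (≥70 good". The missing percent sign is taken as typographical.
- **Acceptability:** "No. of individuals who complete 9/12 visits/total enrolled (≥70 good". Nine of 12 is 75% attendance for an individual.
- **Source of the benchmarks:** "Benchmarks are determined by prior LSC metrics and expectations for recruitment, enrollment, and participation based on prior LSC participants". The next sentence adds that "The metrics we propose are based on study-specific retention efforts", with counselling, relationship building and incentives as examples. No size is given for their effect.
- **Past attendance (Intervention section):** "10-15 individuals are recruited per group and 6-8 attend each session due to the nature of the population (eg, multimorbidity and acute illness". The same section says that "The number of participants per group is determined based on past levels of participation", so this history also sizes the study's own clubs.
- **Eligibility (Inclusion and Exclusion Criteria):** people are excluded for dementia by the AD8 or an earlier diagnosis, for severe hearing or vision loss, or for having neither internet nor telephone.
- **Sample (Data Analysis):** 50 enrolled, with 15% expected to drop out.

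**The concern.** Feasibility is the study's stated purpose, and these are two of its three numerical criteria.

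The enrolment ratio mixes two quantities that a later trial needs separately: how many screened people qualify, and how many of those who qualify are willing. A low value could mean a strict screen, poor uptake or both, and the ratio alone cannot say which.

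The acceptability threshold is presented as resting on LSC experience, yet the experience shown points to a much lower completion rate. The Intervention section plans clubs on the footing that about half the members attend a given session. Textbox 1 expects 70% of enrollees to attend at least three-quarters of sessions. Without a stated link between the two, a result below 70% cannot be read. It might mean that the programme was poorly accepted, or only that the bar stood above routine LSC performance.

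**Working it through.** The plan gives no calculation behind either benchmark, so there is no figure of its own to reproduce. For acceptability, 70% of 50 is 35 people.

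**Enrolment.** Let *u* be the ineligible share of those screened and *c* the share of eligible people who agree. The benchmark measures (1 − *u*) × *c*, so meeting it requires *c* = 0.70 / (1 − *u*). The documents do not give *u*; the values below are assumptions.

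| Ineligible | Agreement needed among eligible | Benchmark value if 70% of eligible agree |
|---|---|---|
| 0% | 70% | 70% |
| 10% | 0.70/0.90 = 78% | 63% |
| 20% | 0.70/0.80 = 88% | 56% |
| 30% | 0.70/0.70 = 100% | 49% |

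Above 30% ineligible the required agreement exceeds 100%.

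**Acceptability: past attendance.** From the Intervention section, the extremes are 6/15 = 40% and 8/10 = 80%. The midpoints give 7/12.5 = 56%. Pairing low with low and high with high gives 6/10 = 60% and 8/15 = 53%.

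**From attendance to completion.** The protocol reports head-counts per session, not completion per member, so the share reaching 9 of 12 has to be modelled. With mean attendance *p* and all members alike, it is P(X ≥ 9) for X ~ Binomial(12, *p*). To let members differ, attendance probability follows Beta(*ps*, (1 − *p*)*s*) with *s* = 1/ρ − 1, where ρ is an assumed between-person correlation. In the last column, 15% attend nothing and the rest are alike at *p*/0.85, giving 0.85 × P(X ≥ 9).

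| Mean attendance | ρ = 0 | ρ = 0.1 | ρ = 0.3 | ρ = 0.5 | 15% attend nothing |
|---|---|---|---|---|---|
| 53% (8/15) | 11% | 22% | 33% | 41% | 24% |
| 56% (7/12.5) | 15% | 26% | 37% | 44% | 32% |
| 60% (6/10) | 23% | 33% | 42% | 48% | 43% |
| 70% (7/10) | 49% | 53% | 57% | 61% | 73% |
| 80% (8/10) | 80% | 74% | 72% | 74% | 85% |

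At 56%, the chance that at least 35 of 50 reach 9 sessions is below 0.1% with ρ = 0 or ρ = 0.3.

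**Mean attendance needed for 70%.** Solving for *p* gives 76.7% at ρ = 0 and 77.2-78.5% for ρ from 0.1 to 0.5. If the planned 15% drop out and attend nothing, 35 of 42.5 stayers (82%) must reach 9 sessions. That needs 81.1% attendance among stayers if they are alike, or 0.85 × 0.811 = 69% over all enrolled. With ρ from 0.1 to 0.5 among stayers, the overall mean needed is about 72-74%.

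**Upper limit.** Whatever the pattern, the share reaching 9 cannot exceed 12*p*/9. At 56% this is 6.72/9 = 75%, reached only if that share attends exactly nine sessions each and everyone else attends none.

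**The case against.** **The 70% is a deliberate uplift.** The protocol says that the benchmarks reflect expectations as well as past metrics, and it names retention efforts. A study may aim above routine service. This stands as a partial answer, but the uplift has no size. The one concrete incentive is tied to data collection ("Participants will receive a gift card for each completed assessment"), and no reward for attending sessions is described. The Intervention section attributes past attendance to illness and sizes the study clubs on it.

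**The history is too coarse to contradict the target.** Head-counts are not completion rates, the 56% comes from pairing midpoints, and the range reaches 80%, where the target is met. This stands as a limit: the model shows a mismatch over most of the range, not at its top.

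**The enrolment wording may be shorthand.** If screened means screened and eligible, the problem disappears. Partners who refer people may also filter beforehand. Neither is stated. Yield per person screened is useful for planning and worth reporting, but it does not measure willingness.

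**Stronger readings that the documents do not support.** A reader might infer that a future trial hangs on these thresholds. Textbox 1 only labels 70% as good, no stop/go rule is stated, and surveys and interviews also inform acceptability. A reader might also take the abstract's reference to lonely participants, with the background prevalence of up to 43%, to mean that the enrolment benchmark is unattainable. The eligibility criteria contain no loneliness requirement, and that prevalence describes older adults in general, not people referred to this study.

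**Conclusion.** Both points hold in limited form.

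As worded, the enrolment benchmark is lowered by every ineligible person screened. With 70% agreement among eligible people it falls short at any ineligible share above zero. How far depends on a share that the documents do not give, so the 10-30% figures are illustrations.

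The acceptability threshold is not supported by the attendance history shown. At the midpoint of that history, about 15-44% would reach 9 of 12, against a target of 70%. The target is met only near the top of the range: at 8 of 10 attending, or at about 7 of 10 if all dropouts attend nothing and the remaining members are alike. These figures rest on the assumed correlations and on head-counts standing in for individual attendance. It would be wrong to call the target impossible, or to say that LSC performing as usual must fail it. Nor does the mismatch show that 9 of 12 is the wrong measure; replacing it with mean attendance would be a matter of preference.

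**What to change.** **Enrolment.** In Textbox 1, define the rate as those who agree divided by those screened and eligible, and report eligible divided by screened as a separate proportion. The cost is one extra reported figure.

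**Acceptability.** Keep completion of 9 of 12 among all enrolled as the measure. Reconcile the Intervention section, the Feasibility Outcomes text and Textbox 1 by restating the threshold in two stated parts: the level that prior LSC participation supports, and an explicit increment for the retention efforts. If 70% is kept, show how those two parts add up to it. The cost is a short piece of work on past LSC participation and, probably, a less ambitious stated target. Both changes are best made before recruitment, planned for July 2025, so that the thresholds are fixed before any data are seen.

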**Primary outcomes**					
	Loneliness	UCLA Loneliness Scale		Likert scale 1-4 (1=never, 4 often). Total from a set of 20 items	
	Apathy	Apathy Evaluation Scale		18 items on 4-point Likert scale Higher scores=increased apathy	
**Secondary outcomes**					
	Cognition	T-MoCA^a^		Global cognition; ≤26=MCI	
	Meaning and purpose	PROMIS-meaning and purpose		4 items; higher scores=higher meaning or purpose	
	Depressive symptoms	Geriatric Depression Scale		15 items; Score of ≥5 suggests depression	
	Social support	MOS Social Support Scale		19 items; perceived social support; higher scores=greater support	
	Physical function	FRAIL Scale		5 items; self-reported fatigue, resistance, ambulation, illness, weight loss	
	Overall health	Global health status		Self-reported physician diagnosis of 9 common conditions	

^a^T-MoCA: telephone Montreal Cognitive Assessment; version 8.1 to be administered at baseline, version 8.2 at 3 months, and version 8.3 at 6 months to reduce practice effect.

Covariates/Demographics to be collected: age, gender, race/ethnicity, education, occupation before retirement, marital status, living arrangements, and social determinants of health (Montefiore version).

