### Data Analysis

The primary purpose of this exploratory project is to test the feasibility of an LSC intervention and to provide estimates of the efficacy of the LSC intervention to inform a future RCT. We will enroll a total sample size of 50 participants and expect an estimated 15% dropout rate. This sample size follows guidelines for pilot studies and is appropriate for exploring feasibility [51]. Descriptive statistics will be used to report sample characteristics, feasibility markers, and measures. Statistical analyses will be conducted using Stata (version 18.5; StataCorp LLC). Repeated-measures ANOVA will be applied to test for overall differences in loneliness and apathy at baseline, 3 months, and 6 months. Secondary outcomes will be analyzed for differences in trends before and after the intervention and associations with changes in loneliness and apathy. We will test whether these measures mediate changes in loneliness and apathy from baseline using linear regression models.

We will use field notes and memos throughout the qualitative interview process to explore qualitative data. Data will be deductively analyzed using NVivo 15 software.

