The study has potential limitations. As a pilot study, the primary purpose of the proposed study is to test the feasibility of vGRT and provide preliminary efficacy data to improve loneliness and apathy. The pilot will include a single-arm and participants will not be randomized. The study will lay the groundwork for a future RCT of a LSC intervention to improve cognition in older adults. LSC engagement to date is consistent with prior work that has shown older adults can be exceptionally adherent to technological interventions with thoughtful planning and troubleshooting [52]. It is possible that technology access varies across populations and may affect the recruitment of diverse participants. We plan to collect quantitative and qualitative data regarding technology access which will inform future studies of LSC interventions. Future studies might also explore the provision of technology (eg, a tablet to allow access to videoconferencing software) to further promote access and participation. Currently, LSC is limited to 4 languages (English, Spanish, Cantonese, and Mandarin), which may exclude participants who speak other languages. In addition, the current study is restricted to individuals with and those without cognitive impairment and excludes individuals with dementia based on the AD8 assessment. The feasibility of LSC in its current format of virtual delivery, in a medium-sized group setting, with a nonclinical facilitator in individuals with advanced dementia remains an area of opportunity for future research.

In summary, this study will provide valuable data for a future RCT of a vGRT intervention to improve loneliness and apathy in community-dwelling older adults. If successful, the intervention can be widely scaled as a nonpharmacological intervention to prevent cognitive decline and promote social engagement in aging. The proposed methods to leverage community-based partnerships to establish and deliver effective interventions within communities can serve as a model for more community-engaged aging research.

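### The fixed T-MoCA version order aliases form difficulty with mean cognitive change in this single-arm study; a counterbalanced order would remove that component at little cost

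*Protocol article*

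**What the plan says.** The Table 2 footnote on the T-MoCA sets one version per visit for every participant: "version 8.1 to be administered at baseline, version 8.2 at 3 months, and version 8.3 at 6 months to reduce practice effect". The visits come from Data Collection: "Assessments will be collected via telephone at baseline, 3 months, and 6 months post RT". The Discussion confirms that no concurrent group follows the same schedule: "The pilot will include a single-arm and participants will not be randomized".

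T-MoCA is listed as a secondary outcome. The Secondary Outcomes section gives these measures a mediating role: "Secondary outcomes will be examined as potential mediators of effects between RT, loneliness, and apathy". Data Analysis commits to two uses of them, a before/after comparison with associations, "Secondary outcomes will be analyzed for differences in trends before and after the intervention and associations with changes in loneliness and apathy", and a mediation analysis, "We will test whether these measures mediate changes in loneliness and apathy from baseline using linear regression models".

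The Primary Outcome section concedes that the study has no power for cognition and that three to six months may not be long enough for it to move. The Cognition section supports the T-MoCA by comparison with the in-person MoCA. It says nothing on whether 8.1, 8.2 and 8.3 are equally difficult.

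**The concern.** Alternate forms are a sensible guard against practice effects. Giving them in one fixed order, however, makes the baseline-to-3-month contrast also a contrast of 8.1 with 8.2, and the baseline-to-6-month contrast one of 8.1 with 8.3. A two-arm trial on this schedule could subtract a common form effect; a single-arm study cannot. A slightly harder later form would look like decline, and a slightly easier one like improvement.

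What is at stake is the mean T-MoCA change and whatever is computed from it: an indirect effect that multiplies that mean change by a slope, or a cognition estimate carried into the future RCT, which the Discussion says will target cognition. The order is a data-collection rule stated in the article, so a later analysis plan cannot repair it from the trial's own data.

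**Working it through.** The article states no figure on this point to reproduce. The check has four parts.

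**1. Can time and form be separated?** Inputs: three visits, three forms, one order for all (Table 2 footnote), and about 42 completers from "We will enroll a total sample size of 50 participants and expect an estimated 15% dropout rate" (50 × 0.85 = 42.5, taken as 42).

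Model: score = participant + time + form + error. The design matrix has 42 participant columns, 2 time columns and 2 form columns, 46 in all, over 42 × 3 = 126 rows.

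- Fixed order: the two form columns equal the two time columns, so the rank is 44 of 46. Both form effects are aliased with time.
- Three-sequence Latin square, or all six orders: the rank is 46 of 46. Time and form are separately estimable.
- The variance of a time contrast under either balanced scheme with form in the model is 0.0476σ², equal to 2/42 = 0.0476σ² without form terms. The cost is 2 degrees of freedom.

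**2. What does the aliasing bias?** Let d be the form difference, the same for every participant, and ΔM the change on a common form. The observed change is ΔM + d.

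- Mean change: E(ΔM) + d, biased by d.
- Slope of loneliness or apathy change on T-MoCA change: cov(ΔY, ΔM + d) / var(ΔM + d) = cov(ΔY, ΔM) / var(ΔM), unchanged. The intercept absorbs the shift.
- An indirect effect formed as mean change × slope b: (E(ΔM) + d) × b, biased by d × b.

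**3. How large could it be?** Assumptions that are not in the article: within-person change SD of 2 to 3 points, form difference of 0.5 or 1.0 point on the 22-point scale, no true change, two-sided 5% paired t-test, n = 42. With SE = SD/√42 and noncentrality = d/SE, the noncentral t gives the chance of a false significant result (nominal 5%):

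| SD | SE | d/SE at 0.5 | Rejection at 0.5 | d/SE at 1.0 | Rejection at 1.0 |
|---|---|---|---|---|---|
| 2.0 | 0.309 | 1.6 | 35% | 3.2 | 89% |
| 2.5 | 0.386 | 1.3 | 24% | 2.6 | 72% |
| 3.0 | 0.463 | 1.1 | 18% | 2.2 | 56% |

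If all 50 were assessed, the ranges would be 21% to 41% and 64% to 93%.

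**4. What does counterbalancing do to individual change scores?** Suppose form effects of 0, 0.5 and 1.0. The first-to-second-visit form differences over the three sequences are +0.5, +0.5 and −1.0. Their mean is 0 and their variance is (0.25 + 0.25 + 1.00)/3 = 0.5. With a change SD of 2.5 and form left out of the model, the SD becomes √(6.25 + 0.5) = 2.60. The bias in the mean is gone and the added noise is small.

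**The case against.** The strongest reply is that little depends on this outcome. The article says it has no power for cognition, moves the primary outcomes to loneliness and apathy for that reason, and rests its hypothesis on feasibility and acceptability. None of those is touched. This stands, and it limits the severity.

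Four stronger readings are tempting, and the article does not support them.

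- **The mediation analysis as a whole is invalid.** Part 2 of the working shows otherwise: a shift common to everyone leaves the slopes unbiased. Only quantities that use the mean change are exposed.
- **The forms do differ.** Nothing in the article suggests this. The percentages follow from assumed values, and from an assumed paired t-test, since the article names no test for the mean change in secondary outcomes.
- **Form and time can never be separated.** The trial's data cannot do it, but external equating data could, and such evidence may exist in sources not shown.
- **Counterbalancing would turn mean T-MoCA change into a clean efficacy estimate for the RCT.** With one arm, residual practice, ageing and regression to the mean stay mixed with the intervention. The article also does not say that T-MoCA change will size the RCT.

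A further fair objection is that the remedy has a price. A single baseline form keeps raw baseline scores comparable between people and against the below-18 cut-off in the Cognition section. Under counterbalancing, with the 0/0.5/1.0 example, two people could differ by up to 1 point from form alone. A form term in the T-MoCA model also does not clean up regressions where T-MoCA change is a predictor; those need a sequence term.

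What survives is the aliasing itself and the planned before/after analysis that it affects. Low power for a real effect gives no protection against a systematic shift being read as one.

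**Conclusion.** The point holds in a limited form. Under the stated order, any form-difficulty difference is inseparable, within this study's data, from mean T-MoCA change at 3 and 6 months. That conclusion follows from the footnote and the single-arm design and needs no outside fact. Its practical size is unknown: the 18% to 35% and 56% to 89% figures hold only if the forms differ by 0.5 or 1.0 point, the change SD is 2 to 3 points, about 42 people complete and a paired t-test is used. The slope result assumes that the form shift is the same for everyone. Severity is minor to optional, because the outcome is secondary and unpowered. It is worth acting on because the fix is cheap and works only if it is in place before the first baseline assessment.

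**What to change.** Before recruitment, replace the footnote's fixed order with a counterbalanced one. Assign each participant at enrolment, from a preset list in REDCap, to one of three Latin-square sequences (8.1-8.2-8.3, 8.2-8.3-8.1, 8.3-8.1-8.2) or to one of all six orders. No participant repeats a form, so the practice-effect aim is kept.

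Include form as a fixed effect in the T-MoCA change model. Where T-MoCA change is a predictor of loneliness or apathy change, include form sequence as a covariate. Three sequences use 2 degrees of freedom there and six use 5, which favours three at this sample size.

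Report mean T-MoCA change as descriptive in any case, and state that counterbalancing removes only the form component. If the fixed order is kept, cite evidence that the three versions are equivalent and apply the same descriptive label.

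Cost: an assignment list, extra model terms, a check by assessors of which form is due, and slightly less comparable raw baseline scores. No added visits or participants.
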